#### Secondary outcome measures

The following measures will be used to assess secondary outcomes. Each measure will be administered at T0, T1, T2 and T3 (see Table 1).Montgomery-Asberg Depression Rating Scale (MADRS) [52]. A gold standard, psychometrically sound interviewer-rated scale to assess depression symptoms.Young Mania Rating Scale (YMRS) [53]. A gold standard, psychometrically sound interviewer-rated scale to assess manic symptoms.Quick Inventory of Depressive Symptomatology-Self-Report (QIDS-SR) [54]. A self-report measure of depression symptoms with high internal consistency (*α* = 0.87), that correlates highly with established clinician-rated scales including the Hamilton Rating Scale of Depression (*r* = 0.86) [54].Depression Anxiety Stress Scale (DASS-21) [55]. A valid and reliable self-report measure of depression, anxiety and stress (total scores and the latter two sub-scales will be used).Functioning Assessment Short Test (FAST) [56]. An interviewer-rated measure evaluating functional impairment across six different domains (autonomy, occupational functioning, cognitive functioning, financial issues, interpersonal relationships, leisure time), validated in patients with BD. The measure has excellent test-retest reliability and internal consistency (*α* = 0.95) [57, 58].Pittsburgh Sleep Quality Index (PSQI) [59]. One of the most widely used self-report measures of sleep quality. The components and items have demonstrated strong internal consistency; global and component scores have been shown to be stable over time [59].Sleep, Circadian Rhythms and Mood questionnaire (SCRAM) [60]. A self-report measure to assess overlap between sleep, circadian rhythms and mood. Preliminary psychometric analyses indicate adequate test-retest reliability and good internal consistency (*α* = 0.80).Relapse. The MINI [37] will be conducted at each assessment to determine illness episodes. The Time to relapse measure (TIME) [61] assesses relapse or time to intervention, with intervention defined as initiation, discontinuation, or dose adjustment of a treatment, initiation of psychotherapy or electroconvulsive therapy, visit to an emergency provider or hospitalisation in response to new mood symptoms.

#### Other outcome measures and mechanism variables

The following measures will be administered at T0, T1, T2 and T3 (see Table 1), with the exception of the Resource Use Questionnaire (administered at T0, T2 and T3 in order to standardise timeframe assessment for economic analyses).Resource Use Questionnaire (RUQ, unpublished). Although differences in service use are not formally hypothesised as an outcome of the intervention, the self-reported RUQ assesses for any differences in mental health service utilisation between groups before, during, and following the intervention. To derive costing for the economic analysis, this study will use a purpose designed RUQ, which is largely based on previous RUQs used by the study team in other mental health economic evaluations. The RUQ was modified for the international context of the study, assessing direct health care costs (including out-of-pocket costs) and productivity costs. RUQ information will be supplemented by Australian Government Medicare data and Pharmaceutical Benefits Schedule for Australian participants.Assessment of Quality of Life-Eight Dimension (AQoL-8D) [62]. A self-report measure to assess health-related QoL for use in economic evaluations that has been comprehensively validated and demonstrated high test-retest reliability [63] .Five Facet Mindfulness Questionnaire (FFMQ) [64]. A self-report measure of the dispositional tendency to be mindful in daily life. The 39-item measure has satisfactory internal consistency and demonstrates good sensitivity to change [65–67].Self-Compassion Scale (SCS) [68]. A self-report measure assessing the degree of self-compassionate responding towards oneself during hard times. A recent examination of the 26-item measure indicated it is a psychometrically valid and theoretically coherent measure of self-compassion [69] . Excellent internal consistency (*α* = 0.89) for the total score was demonstrated in a bipolar sample [70].Difficulties in Emotion Regulation Scale-16 item (DERS-16) [71]. A self-report measure to assess overall emotion regulation difficulties. The measure has excellent internal consistency (*α* = 0.92) and good test-retest reliability [71].Ruminative Response Scale (RRS-10) [72]. A self-report measure of tendency to ruminate, with adequate internal consistency and test-retest reliability.Responses to Positive Affect Scale (RPA) [73]. A self-report measure to assess rumination and dampening regulation strategies. Tests of convergent validity support associations between sub-scales and mood measures, and acceptable internal consistency was established in a bipolar sample [74].Nonattachment to Self Scale (Whitehead et al.: Letting go of self: nonattachment-to-self and its relationship to depression, anxiety and stress. Submitted). A self-report measure to assess the degree of dispassion/non-attachment to self-concept. The initial validation study (unpublished) of the scale demonstrated good internal consistency (*α* = 0.86), and robust correlations with other constructs in expected directions (e.g., mindfulness for convergent validity; depersonalization for discriminant validity).Depressive Experience Questionnaire Self-Criticism Six-Item Scale (DEQ-SC6) [75]. A self-report measure to assess trait self-criticism, with adequate internal consistency (up to *α* = 0.84) and expected associations with pertinent constructs (e.g., emotional distress).Short revised Almost Perfect Scale (SAPS) [76]. A self-report measure to assess perfectionism, with adequate internal consistency (up to *α* = 0.87). Convergent and discriminant validity was demonstrated with other indicators of perfectionism; as was criterion-validity in terms of associations with other constructs (e.g., conscientiousness, neuroticism, emotion regulation and depression).Adherence to Medication. A self-report question with five response options regarding degree of adherence to medication over the past month.User feedback and engagement. Participants are invited to provide feedback about the program immediately post-treatment. Usage of the site, and frequency/duration of application of skills/knowledge is assessed via self-report at the three major assessment time points (see Table 1). Upon completion of the post-intervention assessments, a subset of participants from each arm will be selected to participate in a recorded qualitative phone interview (with an investigator who is independent of study assessments) regarding their engagement with, and experience of the intervention.Program usage. This is tracked automatically by the website, and data will be used to develop an algorithm operationalising use/adoption, which combines activity completion and active engagements with the intervention [77].Reasons for discontinuation from study. Participants requesting to discontinue their participation will be asked (via a brief phone call from the trial coordinator) for main reasons for discontinuation, with any adverse events documented.

### Statistical analysis plan

Sample size was determined by power analysis using G*Power 3. Analyses were conducted on the primary endpoint (Brief QoL.BD score) at T1 relative to baseline. Based on our pilot study (intent-to-treat *d* = 0.52), and Brief QoL.BD change in comparable RCTs [22, 51], a between-group effect size of *d* = 0.4 was conservatively estimated. This small-to-moderate effect size is comparable to effect sizes found for adjunctive CBT on a range of outcomes in BD [78], and therefore can be considered a clinically important difference given the new intervention is low intensity, low cost, and high access. A sample size of 200 (100 in Mindfulness for Bipolar 2.0 and 100 in Psychoeducation for Bipolar) would provide at least 80% power (1-*β*) to detect an effect of this size at α = 0.05 (two-tailed). Attrition at immediate follow-up was conservatively estimated at 33% based on attrition rates in the pilot study and our earlier RCT of a web-based intervention for BD [39], so *N* = 300 randomised participants are required to generate the required sample size of 200 for the primary analysis.

#### Statistical analysis of primary outcome

Changes from baseline to immediate post-test in QoL.BD scores are hypothesised to be significantly greater in the Mindfulness versus Psychoeducation group. Statistical analyses will be conducted in accordance with the International Conference on Harmonization E9 statistical principles. All treatment-related effects will be estimated using intention-to-treat: all randomised participants will be analysed. We will attempt to follow and assess all participants regardless of level of usage of the site during the intervention period (with the exception of those explicitly discontinuing, or being withdrawn on ethical grounds).

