#### Sensitivity analysis of primary outcome

In order to corroborate the robustness of the primary outcome, the following sensitivity analyses will be performed:Per protocol analysis: estimation of the treatment effects in those participants who actually receive the intervention. For analytic purposes, these analyses will be restricted to participants who complied with the treatment protocol, defined as (i) completed all assessments required for the analysis, and (ii) received a minimal dose of the interventionIntention to treat multivariate regression analysis with imputation, and adjusting for the baseline variables used to impute missing data. For subjects with missing data at either time- point, scores will be imputed using multiple imputation with 20 resamples, and imputing baseline variables age, gender, diagnosis, number of episodes, depression symptoms, country of residence and any relevant data collected post-randomisation (specific analytic method will depend on patterns of missingness in the data). Missing data will be imputed using predictive mean matching, using the 10 nearest neighbours.As in (b) above, but using only observed data.

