#### Moderators of treatment effects

Although no baseline moderators are predicted to explain significant variance in outcome (and consequently stratification is not used in allocation), a signal across standard baseline variables (age, gender, diagnosis, number of episodes, depression symptoms, and country of residence), and the putative mediating variables (above) will be explored. Potential confounds of medication use/changes and use of structured psychological interventions during follow-up will be tracked.

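### The primary effect is stated as a difference in change with no baseline covariate; naming baseline Brief QoL.BD as a covariate would gain power at no cost in participants

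*Protocol article*

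**What the plan says.** The protocol article puts the primary contrast on change in three places. The section on the trial's primary hypothesis predicts a baseline-to-endpoint improvement. The sample-size paragraph under *Statistical analysis plan* says "Analyses were conducted on the primary endpoint (Brief QoL.BD score) at T1 relative to baseline". The section *Statistical analysis of primary outcome* says "Changes from baseline to immediate post-test in QoL.BD scores are hypothesised to be significantly greater in the Mindfulness versus Psychoeducation group". None of these names a model or a covariate.

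Adjustment enters under *Sensitivity analysis of primary outcome*. Analysis (b) is a regression after multiple imputation that adjusts for the variables used to impute, and (c) repeats it on observed data. The variables named are "baseline variables age, gender, diagnosis, number of episodes, depression symptoms, country of residence", followed by an open-ended clause covering data gathered after randomisation. Baseline Brief QoL.BD is not named, and that clause cannot cover a baseline score.

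The T0 score is available. Table 1 schedules it online at baseline, and *Time trend analysis of QoL* uses it in a mixed model, but only for the secondary question. The analysis section for secondary outcomes carries the primary method over to the other scales.

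The power statement is: "a between-group effect size of *d* = 0.4 was conservatively estimated"; "A sample size of 200 (100 in Mindfulness for Bipolar 2.0 and 100 in Psychoeducation for Bipolar") "would provide at least 80% power" "to detect an effect of this size at α = 0.05 (two-tailed"). It does not say which SD standardises d and contains no baseline-to-T1 correlation.

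**The concern.** The baseline value of a scale is usually the best single predictor of its value five weeks later. A comparison of change scores uses that value, but with its coefficient fixed at 1. Regression on baseline estimates the coefficient instead, so the residual variance is as small as a linear use of baseline allows. When the correlation is below 1, the change-score comparison discards some precision.

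The article fixes other analysis details closely: the number of imputations, the imputation method, the number of neighbours and a covariate list. The one variable most likely to predict the outcome is missing from that list, and adjustment of any kind is kept for the sensitivity analyses. What is at stake is power and interval width for the primary effect and, because the method is copied, for each secondary scale.

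**Working it through.** **Inputs from the protocol article.** d = 0.4, two-sided α = 0.05, 100 analysable per arm, 33% attrition, 300 randomised (*Statistical analysis plan*); validation-sample SD of the total score 8.76 (*Primary outcome measure*). **Assumed:** the T0–T1 correlation ρ, shown as a range, and equal variance σ² at the two times.

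**Step 1: reproduce the plan's figure, with no adjustment.**
- Normal approximation: n per arm = 2(1.960 + 0.842)²/0.4² = 98.1, so 99.
- Noncentral t, noncentrality 0.4 × √(100/2) = 2.83: power 80.4% at 100 per arm (79.97% at 99).
- Attrition: 200/0.67 = 298.5, so 299; the plan uses 300.

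The stated 200 and 300 are reproduced.

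**Step 2: variances.**
- Change score: Var(T1 − T0) = 2σ²(1 − ρ).
- Regression of T1 on arm and T0: residual variance σ²(1 − ρ²).
- Ratio: (1 − ρ²)/[2(1 − ρ)] = (1 + ρ)/2, which is below 1 for every ρ below 1.

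**Step 3: power if d = 0.4 is on the change-score SD.** The effective standardised difference becomes 0.4/√[(1 + ρ)/2]. At ρ = 0.5 this is 0.4/√0.75 = 0.462. Power is by noncentral t on 197 degrees of freedom (200 − 3). The last column is 98.1 × (1 + ρ)/2, rounded up.

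| ρ (assumed) | Variance ratio | Change score | Baseline-adjusted | n per arm for 80%, adjusted |
|---|---|---|---|---|
| 0.3 | 0.65 | 80.4% | 93.7% | 64 |
| 0.5 | 0.75 | 80.4% | 90.1% | 74 |
| 0.7 | 0.85 | 80.4% | 86.3% | 84 |
| 0.9 | 0.95 | 80.4% | 82.3% | 94 |

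A simulation of 4,000 trials per setting agrees. Change score against adjusted: 80.0% and 93.2% at ρ = 0.3; 80.4% and 89.5% at 0.5; 81.1% and 86.5% at 0.7.

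**Step 4: the other reading of d.** If d = 0.4 were on the raw-score SD (0.4 × 8.76 = 3.5 points), the effective differences would be 0.4/√[2(1 − ρ)] for change and 0.4/√(1 − ρ²) for the adjusted analysis.

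| ρ (assumed) | Change score | Baseline-adjusted |
|---|---|---|
| 0.3 | 66.2% | 83.9% |
| 0.4 | 72.9% | 86.7% |
| 0.5 | 80.4% | 90.1% |
| 0.7 | 95.3% | 97.6% |

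On either reading the adjusted analysis has the higher power at every ρ shown.

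**The case against.** The strongest reply is that the article never calls the primary comparison unadjusted. The sentence on change is a hypothesis, and a regression of T1 on arm and baseline tests that same hypothesis. The Abstract and *Primary outcome measure* define the outcome as the T1 score, the natural dependent variable for such a regression, and a full protocol or SAP that is not shown may specify it. This stands in part: a reader might infer that a change-score test has been fixed, and the text does not go that far. What it does do is give a covariate list, place adjustment only in the sensitivity analyses and leave the baseline score off the list. That is more than silence.

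A second reply is that sensitivity analysis (b) imputes scores missing at either time point, so the T0 score is already in the analysis and the six named variables are additional. That is possible. But being a variable to be imputed does not make the score a covariate in the outcome regression, and one added term would settle it.

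Three stronger readings are tempting, and the document does not support them.

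- *The 80% power is at risk.* It is reproduced without adjustment. It falls short only if d is on the raw-score SD and ρ is below about 0.5, and the article states neither. Its wording points towards the change scale, since the analyses were of T1 relative to baseline and d drew partly on Brief QoL.BD change in comparable trials.
- *The plan rejects adjustment because it expects no moderators.* The relevant sentence is "Although no baseline moderators are predicted to explain significant variance in outcome (and consequently stratification is not used in allocation"). It explains only the absence of stratification and says nothing about covariates.
- *Chance baseline imbalance biases the change score.* Under randomisation the change-score comparison is unbiased, and its standard error already reflects chance baseline differences. This is the efficiency point again and not a separate defect.

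**Conclusion.** The point holds as an efficiency and pre-specification recommendation. It is neither an error in the sample size nor a challenge to validity; a change-score analysis, if that is what is intended, would be valid.

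With d = 0.4 on the change-score SD and 100 per arm, adjustment adds about 10 percentage points of power at ρ = 0.5, 6 at ρ = 0.7 and 2 at ρ = 0.9. The gain therefore depends on a correlation that the article does not report, and it is small if that correlation is very high. The (1 + ρ)/2 ratio also assumes equal variances at T0 and T1. Without that assumption the size of the gain changes but not its direction, apart from the one degree of freedom, because the change score is the special case with the slope held at 1.

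**What to change.** - Specify the primary analysis as T1 Brief QoL.BD regressed on arm and baseline Brief QoL.BD, or as an equivalent repeated-measures model with a common baseline mean. The arm coefficient still answers the stated hypothesis about change.
- Name baseline Brief QoL.BD explicitly among the covariates in sensitivity analyses (b) and (c).
- Apply the same rule to each secondary scale with its own baseline value.
- State which SD standardises d = 0.4, so that the power statement can be read on one scale.

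If the full protocol or SAP already specifies this model, it is enough to bring the published text and the registry entry into line with it. The cost is wording, settled before unblinding, and one degree of freedom per model. No further participants or data are needed, because Table 1 already schedules the outcome scales at T0.

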### Risk management

Risk management procedures have been developed through our experience with other online interventions and websites for BD [22, 39–43] and through consultation with the *CREST.BD* Community Advisory Group. Procedures pay particular attention to suicide risk, distinguish between solicited and spontaneously reported events, and are reviewed weekly during the trial by the study’s executive committee. To minimise impact of any adverse events, being under the care of a medical practitioner is an inclusion criterion, and participants consent to this professional potentially being contacted by the researchers as part of a ‘red flag decision tree’ (detailed below). The informed consent statement explains that the medical practitioner or local emergency department remains the participant’s first point of contact. Both the pre-registration page and informed consent statement highlight participants’ central role in their own safety and wellbeing, emphasising that the website does not act as an emergency service, and that the website is not monitored in real time. Links to emergency resources will be provided on the website (e.g., *unsuicide.**wikispaces.com*).

Participants will be withdrawn from the trial if their participation compromises clinical care as determined by the study’s executive committee. On a case-by-case basis, this might include hospital admission, acute hypomania or mania, psychotic symptoms or active suicidal intent.

Adverse events will be monitored via questions at post-test and both follow-up time points, and any adverse events incidentally reported through participant contact with coaches, forum posts, or assessments will also be recorded. Severity of any adverse events, and causal relationship to the trial will be assessed through participant self-report and logged. Adverse events will be reviewed at monthly executive meetings and 6-monthly meetings of the independent trial committee (who will also explore patterns of adverse events by condition). Serious adverse events suspected or known to be related to participation in the trial will be reported to Swinburne University of Technology Human Research Ethics Committee.

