#### Secondary outcome measures

Treatment-related change in secondary outcomes analyses will be identical to those described above for the primary outcome. It is anticipated that relative to Psychoeducation, the Mindfulness condition will be associated with improvement in three outcomes: (a) self-rated state anxiety (DASS-Stress, DASS-Anxiety), (b) self-rated depression (QIDS-SR) and (c) clinician-rated depression (MADRS). It is also anticipated that relative to Psychoeducation, the Mindfulness condition will be associated with decreased dropout attrition.

Analysis of treatment-related change in remaining secondary outcomes will be exploratory. Time to first relapse will be analysed using multivariate survival analysis [79].

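### Participants withdrawn from the trial on ethical grounds are exempted from follow-up, so a probably small set of outcomes is left uncollected for reasons related to outcome

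*Protocol article*

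**What the plan says.** Protocol article, Statistical analysis of primary outcome: "All treatment-related effects will be estimated using intention-to-treat: all randomised participants will be analysed". The next sentence says the team will try to follow and assess everyone whatever their use of the site, "with the exception of those explicitly discontinuing, or being withdrawn on ethical grounds".

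Protocol article, Risk management: "Participants will be withdrawn from the trial if their participation compromises clinical care", as judged by the executive committee. "On a case-by-case basis, this might include hospital admission, acute hypomania or mania, psychotic symptoms or active suicidal intent". The withdrawal described is from the trial, not only from the online program.

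Protocol article, Sensitivity analysis of primary outcome: where a score is missing, "scores will be imputed using multiple imputation with 20 resamples", using baseline variables and any relevant data gathered after randomisation. "Missing data will be imputed using predictive mean matching, using the 10 nearest neighbours". The other sensitivity analyses are an observed-data version and a per-protocol version. The time trend analysis of QoL is a mixed model on all four time points.

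Relapse is a secondary outcome. The MINI "will be conducted at each assessment to determine illness episodes", and the TIME measure counts relapse or an intervention, including hospitalisation, made in response to new mood symptoms. "Time to first relapse will be analysed using multivariate survival analysis".

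**The concern.** The grounds on which someone may be withdrawn overlap with what the trial measures: relapse, mania, depression and functioning. If those withdrawn are then not assessed, their data are missing because of the outcome. An analysis set that contains everyone randomised does not help much if the plan has decided in advance not to seek the outcomes of a selected group.

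Two things are at stake. The arm with more such withdrawals looks better than it was if the unseen outcomes are poor. And for time to first relapse, a person withdrawn for a mood episode has no later MINI; unless that episode is recorded as an event, a real relapse is lost. A fuller analysis plan cannot recover data that the protocol says will not be sought.

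**Working it through.** **The plan's own figure.** For d = 0.4, two-sided α = 0.05 and 80% power, the normal approximation gives n = 2(1.960 + 0.842)²/0.4² = 98.1, so 99 per arm. The t-test gives 100 per arm, with power 80.4%. Attrition of 33% gives 200/(1 − 0.33) = 298.5, so 299; one third gives 300. The stated 200 analysed and 300 randomised are reproduced. The point disputes no figure.

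**Who is lost.** The article names no ground for withdrawal by the team other than those in Risk management, so reading the ethical grounds in the analysis section as these is the natural inference, though still an inference. No section provides for outcome assessment after such a withdrawal. The discontinuation call in Other outcome measures and mechanism variables is for participants who ask to stop, and covers reasons and adverse events.

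**Do the stated analyses repair it?** Predictive mean matching fills a gap with an observed score from a followed participant who has a similar predicted value. It works if withdrawn people resemble followed people with the same recorded data. Data collected after randomisation can help in part, but someone withdrawn before the 5-week assessment has only the baseline outcome assessment. The imputation is also listed only as a sensitivity analysis. The mixed model needs the same kind of missing-at-random assumption. Neither the observed-data nor the per-protocol version addresses outcome-related loss.

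**Bias in the arm difference.** Let w1 (Mindfulness) and w0 (Psychoeducation) be the shares withdrawn and not followed, and let their unseen mean lie D SD below that of those who remain. The mean of the remaining participants exceeds the all-randomised mean by w × D in each arm, so

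bias = D × (w1 − w0).

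The article gives neither w nor D; all values below are assumptions. With 150 randomised per arm, 2% is 3 people and 10% is 15. Points use the SD of 8.76 from Primary outcome measure.

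| w1 vs w0 | D = 0.5 | D = 1.0 | D = 1.5 | In points, lowest to highest | Share of d = 0.4 |
|---|---|---|---|---|---|
| equal | 0 | 0 | 0 | 0 | 0 |
| 5% vs 2% | 0.015 | 0.03 | 0.045 | 0.13 to 0.39 | 4% to 11% |
| 10% vs 5% | 0.025 | 0.05 | 0.075 | 0.22 to 0.66 | 6% to 19% |
| 10% vs 2% | 0.04 | 0.08 | 0.12 | 0.35 to 1.05 | 10% to 30% |

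Swapping the arms reverses the sign. With 100 analysed per arm, the standard error is √(2/100) = 0.141 SD. A bias of 0.04 SD shifts the test statistic by 0.28 and raises the two-sided type I error from 5% to 5.9%; a bias of 0.12 SD shifts it by 0.85 and raises it to 13.6%.

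**Can balance be presumed?** Not safely. The article predicts less dropout under Mindfulness, and under Mechanism analyses expects Psychoeducation to act on mania, depression and relapse through medication adherence and rhythm stabilisation. Those are arm-specific routes to the states that may lead to withdrawal. They do not show that committee withdrawals will in fact differ.

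**Relapse.** No size is computed, because the article gives no relapse rate and no censoring rule.

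**The case against.** The strongest case is that the rule is narrower than it looks, and much of it stands.

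- A reader might infer that everyone who becomes manic, is admitted, or becomes psychotic or suicidal goes missing by rule. The article does not say that. The test is whether participation compromises care; the listed states are examples that may meet it. The schedule repeats the MINI with the C-SSRS, the YMRS and the MADRS at every follow-up, so the design expects to keep and assess many who relapse. Only the non-follow-up of those actually withdrawn is fixed.
- A reader might see a flat contradiction with intention-to-treat. That is too strong: the exception is stated openly, and imputation could still place everyone in the analysis. The rule undermines the aim without contradicting the sentence.
- A reader might infer that relapsers are censored on withdrawal. No section says so. The committee must know of an episode to act on it, adverse events are logged, and TIME counts mood-related hospitalisation, so the onset may well be on file. Censoring detail also commonly sits in an analysis plan that is not shown.
- Self-rated quality of life need not be low in hypomania or mania, so a large deficit on the Brief QoL.BD is not assured.
- Participants enter out of episode and the primary endpoint is at 5 weeks, so few may be withdrawn before it.

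What the objection does not remove is the stated decision not to seek outcomes from those withdrawn.

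**Conclusion.** The point holds in a limited form. The follow-up exemption, read with the withdrawal rule, leaves outcomes uncollected for reasons related to outcome in a group of unknown and probably small size. This weakens the intention-to-treat aim, and the analyses described cannot be relied on to make it good.

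Bias in the primary comparison is zero if withdrawal rates and deficits are balanced. It is 0.015 to 0.12 SD (0.13 to 1.05 points) under the unequal rates assumed above, and favours the arm with more withdrawals. The top of that range needs both 10% vs 2% and a deficit of 1.5 SD, neither of which the article supports or excludes. The risk is clearest for relapse and symptom outcomes and less certain for self-rated quality of life. The conclusion rests on equating the ethical grounds in the analysis section with those in Risk management. It is worth correcting because unsought outcomes cannot be recovered later; it does not show that the primary result will be materially biased.

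**What to change.** 1. Leave the committee's clinical withdrawal decision as it is, and state separately what stops: the online program, or data collection.
2. Under Statistical analysis of primary outcome, replace the blanket exemption for ethical withdrawals with continued attempts at the 5-week, 3-month and 6-month assessments. The minimum set is the Brief QoL.BD and relapse status. Exceptions are a participant who withdraws consent for data, or a committee judgement that contact itself compromises care.
3. For time to first relapse, where the reason for withdrawal meets the article's own definition (a MINI episode, or a TIME intervention in response to new mood symptoms), count it as an event dated at onset and not as censoring. An admission unrelated to mood symptoms does not meet that definition and should not be counted.
4. Add a missing-not-at-random sensitivity analysis for those still missing, including voluntary discontinuers. One form lowers the imputed scores by a range of amounts set separately by arm, for example 0 to 1.5 SD (0 to 1.5 × 8.76 = 13.1 points), and reports where the conclusion changes.
5. Report the number withdrawn on ethical grounds by arm, with timing and reason.

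The cost is revised protocol and consent wording on continued data collection, a few extra calls by assessors already in place, and one further analysis.
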